## Appendix 2 SUBJECT QUESTIONNAIRE

### 6.2 Data collected in the e-CRF

#### 6.2.1 Baseline Data

The following baseline data will be collected at the enrolment visit:

- Socio-demographic data: age, body weight, height, education level, socioeconomic status, professional categories, country of residence
- Reproductive history
  - Menstrual history
  - Infertility history: primary infertility, duration of infertility, primary reason for infertility, IVF or ICSI for the current parental project,
- Antral follicle count, as available
- Most recent AMH test result performed with ELECSYS AMH Plus from Roche or ACCESS AMH Advanced from Beckman Coulter or LUMIPULSE G AMH from Fujirebio Immunoassay, characteristics of the AMH test (e.g., type of laboratory, date of test)
- Baseline laboratory measurements: follicle stimulating hormone (FSH), Luteinizing Hormone (LH), estradiol, progesterone, thyroid-stimulating hormone (TSH), prolactin, as available
- Any results from imaging techniques and/or pelvic ultrasound as per local protocols, as available

#### 6.2.2 COS Treatment Data

The following data about REKOVELLE® treatment will be collected:

- Individualized dosing regimen: daily dose of REKOVELLE® administered, number of days of treatment
- Use of the algorithm
- Use of the dosing App
- Ovarian stimulation protocol used
- Stimulation day and triggering method for final follicular maturation
- Monitoring of the REKOVELLE® treatment (number and intents of each visit)

### 6.2.3 Follow-up

No visits are mandated or prescheduled as part of the trial. Follow-up information will be collected by the physicians at one single visit scheduled as a part of routine care or may be collected via a telephone interview if a visit does not occur.

The following data will be collected for the 1st cycle with REKOVELLE®:

- Ultrasound results since last visit, as available
- Antral follicle count, as available
- Luteal phase support
- OHSS (including mild/moderate/severe)
- Preventive measures for OHSS:
  - Triggering of final follicular maturation with GnRH agonist and cancellation of fresh embryo/blastocyst transfer
- Oocytes retrieval: number of oocytes retrieved, number of metaphase II (MII) oocytes
- Number of frozen oocytes/embryos/blastocysts
- Freeze all strategy: reasons for freeze all strategy as alternative to fresh embryo transfer
- Fresh embryo/blastocyst transfer: day of embryo/blastocyst transfer, number and quality of embryos/blastocysts transferred
- Frozen embryo/blastocyst transfer (FET): endometrial preparation protocol, date of FET, number and quality of embryos/blastocysts transferred
- Pregnancy outcome: positive hCG, clinical pregnancy, vital pregnancy, ongoing pregnancy
- Pregnancy loss: biochemical pregnancy, spontaneous abortion, elective abortion, ectopic pregnancy, vanishing twin
- Cycle cancelled before oocyte pick-up, Transfer Cancellation, and reason for cycle cancellation:
  - Cancellation before oocyte pick-up (poor ovarian response, excessive ovarian response, any illness which prevents oocyte collection procedure, subject not taking hCG injection at the correct time, subject choice, other)
  - Transfer Cancellation after oocyte pick-up (no oocytes collected, no oocytes fertilised, abnormal fertilisation, abnormal embryo development, no embryo development, OHSS, subject choice, other)
- ADRs serious and non-serious, related / non-related fatal events

### 6.2.4 Trial Termination

The date of trial completion will be recorded in the trial termination form of the e-CRF.

In the event of trial withdrawal, the investigators will be asked to document the date and the reason for trial withdrawal in the trial termination form of the e-CRF.

## 6.2.5 Subject Questionnaire

The subject questionnaire will be completed by the subjects at the clinic after cycle cancellation or before oocyte retrieval.

## 7 SAFETY REPORTING

### 7.1 Definitions

#### 7.1.1 Adverse Event

An AE is any untoward medical occurrence in a subject participating in a trial. It includes:

- Any unfavourable and unintended sign, symptom or disease temporally associated with the use of the REKOVELLE®, whether considered to be caused by the REKOVELLE®.
- Adverse events commonly observed and adverse events anticipated based on the pharmacological effect of the REKOVELLE®.
- Any laboratory abnormality, vital sign or finding from physical or gynaecological examination assessed as clinically significant by the investigator [note: findings from assessments and examinations done during screening are not adverse events, but are recorded as medical history].
- Accidental injuries, reasons for any change in medication (drug and/or dose), reasons for any medical, nursing or pharmacy consultation, or reasons for admission to hospital or surgical procedures.

#### 7.1.2 Serious Adverse Events

Serious Adverse Events during the trial:

| An event is defined as a serious adverse event if it:                                  | Guidance                                                                                                                                                                                                                                                                                                                                                                                                                                                                                                                         |
|----------------------------------------------------------------------------------------|----------------------------------------------------------------------------------------------------------------------------------------------------------------------------------------------------------------------------------------------------------------------------------------------------------------------------------------------------------------------------------------------------------------------------------------------------------------------------------------------------------------------------------|
| Results in death                                                                | Any event resulting in a fatal outcome must be fully documented and reported, including deaths occurring within four weeks after the treatment ends and irrespective of the causal relationship to REKOVELLE®. The death of a subject enrolled in a trial is per se not an event, but an outcome.                                                                                                                                                                                                                                |
| Is life-threatening                                                             | The term life-threatening refers to an adverse event in which the subject was at immediate risk of death at the time of the event. It does not refer to an event, which may have caused death if it were more severe.                                                                                                                                                                                                                                                                                                            |
| Requires in-patient hospitalisation or prolongation of existing hospitalisation | The term hospitalisation means that the subject was admitted to hospital or that existing hospitalisation was extended as a result of an event.
Hospitalisation describes a period of at least 24 hours. Over-night stay for observation, stay at emergency room or treatment on an out-patient basis do not constitute a hospitalisation. However, medical judgement must always be exercised and when in doubt the case should be considered serious (i.e., if case fulfils the criterion for a medically important event). |

| An event is defined as a serious adverse event if it:                      | Guidance                                                                                                                                                                                                                                                                                                                                                                                                                                                                                                                                                                                                                                                                                                                                                                                                                                                                                                                                                                                         |
|----------------------------------------------------------------------------|--------------------------------------------------------------------------------------------------------------------------------------------------------------------------------------------------------------------------------------------------------------------------------------------------------------------------------------------------------------------------------------------------------------------------------------------------------------------------------------------------------------------------------------------------------------------------------------------------------------------------------------------------------------------------------------------------------------------------------------------------------------------------------------------------------------------------------------------------------------------------------------------------------------------------------------------------------------------------------------------------|
|                                                                            | Hospitalisations for administrative or social purposes do not constitute a serious adverse event. Hospital admissions and/or surgical operations planned before trial inclusion are not considered adverse events, if the illness or disease existed before the subject was enrolled in the trial, provided that the condition did not deteriorate during the trial.                                                                                                                                                                                                                                                                                                                                                                                                                                                                                                                                                                                                                             |
| Results in persistent or significant disability / incapacity | Disability / incapacity means a substantial disruption of a person's ability to conduct normal life functions. In doubt, the decision should be left to medical judgement by the investigator.                                                                                                                                                                                                                                                                                                                                                                                                                                                                                                                                                                                                                                                                                                                                                                                                   |
| Is a congenital anomaly / birth defect                       | Congenital anomaly / birth defect observed in any offspring of the subject conceived during treatment with REKOVELLE® (please refer to section 7.3)                                                                                                                                                                                                                                                                                                                                                                                                                                                                                                                                                                                                                                                                                                                                                                                                                                              |
| Is an important medical event                                       | 
Important medical events are events that may not be immediately life- threatening or result in death or hospitalization but may jeopardize the subject or may require intervention to prevent one of the other outcomes listed in the definition above. Examples of important medical events include adverse events that suggest a significant hazard, contraindication or precaution, occurrence of malignancy or development of drug dependency or drug abuse. Medical and scientific judgement should be exercised in deciding whether events qualify as medically important.
 
Important medical events include any suspected transmission of an infectious agent via a medicinal product. Any organism virus or infectious particle, pathogenic or non-pathogenic, is considered an infectious agent. A transmission of an infectious agent may be suspected from clinical symptoms or laboratory findings indicating an infection in a subject exposed to a medicinal product.
 |

### 7.1.3 Causal Relationship to REKOVELLE®

The possibility of whether the REKOVELLE® caused the AE must be classified as follows:

- Reasonable possibility: There is evidence or argument to suggest a causal relationship between REKOVELLE® and the AE. The AE may occur as part of the pharmacological action of the REKOVELLE® or may be unpredictable in its occurrence.

Examples:

- AEs that are uncommon but are known to be strongly associated with REKOVELLE® exposure.
- AEs that are not commonly associated with REKOVELLE® exposure, but the event occurs in association with other factors strongly suggesting causation, such as a strong

temporal association with REKOVELLE® or the event recurs on rechallenge with REKOVELLE®.

- No reasonable possibility: There is no reasonable evidence or argument to suggest a causal relationship between REKOVELLE® and the adverse event.

Examples:

- Known consequences of the underlying disease or condition under investigation.
- AEs common in the trial population, which are also anticipated to occur with some frequency during the course of the trial, regardless of REKOVELLE® exposure.

An Adverse Drug Reaction (ADR), in contrast to an AE, is characterized by the fact that a causal relationship between REKOVELLE® and the AE is at least a reasonable possibility.

## 7.2 Adverse Event Resulting in Fatal Outcome

Any adverse event resulting in a fatal outcome must be fully documented and reported, including deaths occurring within four weeks after the treatment ends and irrespective of the causal relationship to REKOVELLE®. The death of a subject enrolled in the trial is per se not an event, but an outcome. See section 7.5 for reporting.

## 7.3 Congenital Abnormality

Any congenital abnormality discovered in the embryo or fetus during the trial must be fully documented, recorded and reported as a serious adverse event regardless of causality including any congenital anomaly which the Investigator may become aware of after end of trial. See section 7.5 for reporting.

## 7.4 Collection and Recording of Adverse Drug Reactions

REKOVELLE® (follitropin delta) is a recombinant human FSH with a well characterised safety profile documented in pivotal clinical trials. REKOVELLE® has been approved in EU via centralised procedure in December 2016 with a positive benefit-risk balance. Based on this, the scope of the safety data collection of adverse events in this non-interventional observational trial should be limited to collection of adverse drug reactions, both serious and non-serious [19].

This in addition to the report requirements stated in sections 7.2 and 7.3 in the protocol.

All ADRs to REKOVELLE®, whether serious or non-serious, are to be captured in the e-CRF and investigator must record the ADRs in the ADR Log provided in each subject's e-CRF with, as a minimum required, the following information:

- Adverse Drug Reaction
- Date of onset
- Intensity
- Action taken to REKOVELLE®
- Other action taken
- Date of outcome
- Outcome

- Seriousness criteria if applicable
- Short description of ADR (if not serious)

The data collected in the e-CRF for the ADRs is described in detail in the following sections.

Concomitant medication will be collected for all ADRs and Medical History will be collected for all serious ADRs.

### **Adverse Drug Reactions**

Adverse Drug Reaction ADRs should be recorded as diagnoses, if available. If not, separate signs and symptoms should be recorded. One diagnosis / symptom should be entered per record.

If a subject suffers from the same ADR more than once and the subject fully recovers in between the events, the ADR should be recorded separately. If an ADR changes in intensity, a worst-case approach should be used when recording the ADR, i.e., the highest intensity and the longest duration of the event.

*Note:* A procedure is not an adverse event; the reason for conducting the procedure is. Hospitalisation is not an adverse event; the reason for hospitalisation is. Death is not an adverse event, but the cause of death is (an exception is sudden death of unknown cause, which is an adverse event).

### **Date of Onset**

The date of onset is the date when the first sign(s) or symptom(s) were first noted. If the ADR is an abnormal clinically significant laboratory test or outcome of an examination, the onset date is the date the sample was taken, or the examination was performed.

### **Intensity**

The intensity of ADRs must be classified using the following 3-point scale:

- Mild: Awareness of signs or symptoms, but no disruption of usual activity
- Moderate: Event sufficient to affect usual activity (disturbing)
- Severe: Inability to work or perform usual activities (unacceptable)

### **Action Taken to REKOVELLE®**

The action taken to the REKOVELLE® in response to an ADR must be classified as one of the following:

- No change (medication schedule maintained or no action taken)
- Withdrawn
- Dose reduced
- Dose increased
- Not applicable

## Other Action Taken

ADRs requiring therapy must be treated with recognised standards of medical care to protect the health and well-being of the subject. Appropriate resuscitation equipment and medicines must be available to ensure the best possible treatment of an emergency situation.

## Date of Outcome

The date the subject recovered or recovered with sequelae.

## Outcome

The outcome of an ADR must be classified as one of the following:

- Recovered (fully recovered or the condition has returned to the level observed at initiation of trial treatment)
- Recovered with sequelae (resulted in persistent or significant disability / incapacity)
- Recovering
- Not yet recovered
- Fatal

## 7.5 Collection, Recording and Reporting of Serious Adverse Drug Reactions

Serious Adverse Drug Reaction reporting by the Investigator

All serious ADRs (SADRs) must be reported immediately to Ferring Global Pharmacovigilance as soon as it becomes known to the investigator and not later than within 24 hours of their knowledge of the occurrence of a SADR.

The investigator is responsible for submitting the completed SADR Report Form with the fullest possible details within 3 calendar days of his/her knowledge of the SADR.

Serious Adverse Drug Reaction Report Form

The SADR Report Form is included in the e-CRF system and must be completed and submitted according to the instructions provided on the form. In case the e-CRF cannot be accessed and hence the SADR Report Form cannot be filled in within the e-CRF system, a paper SADR Report Form should be used and sent to Ferring Global Pharmacovigilance using the contact details below.

Global Pharmacovigilance, Ferring Pharmaceuticals A/S

mail to: [[contact]](mailto:[contact])

Fax: [name]

SADRs will be reported to the regulatory authorities according to local legislation. The investigator should comply with local legislation for safety reporting.

## Additional Information

Additional information relevant to the SADR such as hospital records, results from investigations, e.g., laboratory parameters (that are not already uploaded in the e-CRF), invasive procedures, scans and x-rays, and autopsy results should be included in SADR narrative text.

The investigator will supply Ferring and the ethics committee with any additional requested information such as results of post-mortem examinations and hospital records.

## **7.6 Follow-up of Adverse Drug Reactions and Serious Adverse Drug Reactions**

### **7.6.1 Follow-up of Adverse Drug Reactions**

The investigator must follow-up on each ADR until it is resolved or until the medical condition of the subject is stable. All such relevant follow-up information must be reported to Ferring. If the event is a chronic condition, the investigator and Ferring may agree that further follow-up is not required.

### **7.6.2 Collection of Serious Adverse Drug Reactions with Onset after End of Trial**

If an investigator becomes aware of a SAE after the end of the trial, and he/she assesses the SAE to have a reasonable possible causality to REKOVELLE® or another product where Ferring is Marketing Authorisation Holder, the case will have to be reported to Ferring, regardless how long after the end of the trial this takes place.

## **8 STATISTICAL METHODS**

### **8.1 Sample Size**

The sample size was planned to ensure that the trial obtains meaningful estimates for the description of REKOVELLE® patterns of use, ovarian stimulation and embryo development outcomes, and safety and subject satisfaction at the 1st cycle with REKOVELLE®.

This trial will be conducted in Nordic Countries (Sweden, Denmark, Norway) and Switzerland with the activation of 15 sites, known to follow-up women undergoing ART and to regularly prescribe REKOVELLE®. Each site will enrol maximum 15 subjects during the predefined inclusion period, until the total 200 subjects initiated with REKOVELLE® treatment enrolment target achieved in a competitive manner.

As the statistical analyses will be purely descriptive, the sample size is not based on any inferential statistical considerations.

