## **STATISTICAL METHODS**

### **Statistical analysis**

This is a descriptive trial. There are no hypotheses to be tested and no inferential statistics will be applied. All descriptions of data will be based on all subjects enrolled in the trial who meet the inclusion/exclusion criteria and who receive at least one dose of REKOVELLE®. Therefore, pregnancy rates will be calculated for all subjects starting stimulation with REKOVELLE®, and mean number of oocytes, embryos, blastocysts etc. will be the mean for all subjects starting stimulation with REKOVELLE®.

Missing data for pregnancy outcomes will be regarded as “no pregnancy”. Missing data for number of oocytes, number of embryos, number of blastocysts, and similar endpoints will be regarded as zero.

The primary endpoint, real-life treatment patterns in first cycle with REKOVELLE® will be extensively described.

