### **Sample size**

The sample size is not based on any inferential statistical considerations. This trial will be conducted in Nordic Countries (Sweden, Denmark, Norway) and Switzerland in Europe, with the activation of 15 sites, known to follow-up women undergoing ART and to regularly prescribe REKOVELLE®. Each site will enrol maximum 15 subjects during the predefined inclusion period, until the total 200 naïve women initiated with REKOVELLE® treatment are enrolled and enrolment target is achieved in a competitive manner.

Considering the total number of fertility centres in those countries and knowing that all these centres prescribe REKOVELLE®, the 15 sites expected to participate in the trial should be sufficiently representative to reflect the variety of practices in those contributing European Countries.

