## 4.3 Limitations of Trial Design

The trial is associated with some methodological limitations commonly found in observational studies:

- Selection Bias

Subjects will be included in the trial by approximately 15 sites known to follow-up women undergoing ART. The participating sites will be selected from private and public practice to represent all existing treatment policies and will be spread across the territory to represent as much as possible the variety of populations in the countries involved. This number of sites expected to participate in the trial may be too limited to be representative and to reflect the variety of practices in the countries involved.

Selection bias is a distortion of evidence or data that arises from the way data are collected. In order to limit bias in the selection of subjects, investigators will be asked to consecutively enrol all subjects who are prescribed REKOVELLE® for IVF/ICSI cycle, have signed informed consent and meet the selection criteria, regardless of other considerations.

To promote consecutive inclusions by investigators, this request will be regularly reminded. In addition, investigators will be asked to include all their eligible subjects to a limit of 15 during the predefined inclusion period, until the objective of 200 inclusions is reached. This procedure aims to have a representative sample of subjects treated with REKOVELLE®, based on real prescriptions, which could vary according to centres, while limiting a centre effect.

- Information Bias

Relying on investigators to fill out the assessment forms might induce the presence of missing data, which can result in bias. Entry of data via e-CRFs will minimise missing or incorrect data thanks to automated queries. Clear instructions and engagement with the trial staff, including appropriate training will minimise the amount of missing data.

- **Confounding Bias**

Confounding bias occurs when the effects of a treatment or the exposition effect of the disease vary by presence/level of another factor (effect modifier). Effect modifiers may be controlled by using stratification in the statistical analysis (subgroup analyses).

- **Lost to follow-up**

In order to assess the existence of attrition bias, the main baseline characteristics of subjects lost to follow-up will be contrasted with subjects having completed the trial. Because of the duration of the trial, the proportion of lost to follow-up subjects might not be high in proportion.

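### Section 8.1 claims 200 women ensure meaningful estimates but states no precision, results are confined to percentages without intervals, and the protocol contradicts itself on whether 15 sites are representative

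*Protocol*

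**What the plan says.** **Sample size.** Section 8.1 opens: "The sample size was planned to ensure that the trial obtains meaningful estimates for the description of REKOVELLE® patterns of use"; the sentence goes on to cover stimulation and embryo outcomes, safety and satisfaction. The same section ends by saying that "the sample size is not based on any inferential statistical considerations". Between the two it gives only logistics: "with the activation of 15 sites", "Each site will enrol maximum 15 subjects during the predefined inclusion period", and competitive enrolment to 200.

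**Reporting.** The outline, under Statistical analysis, says: "There are no hypotheses to be tested and no inferential statistics will be applied". Section 8.2.1 lists number, percentage and number missing for categorical variables, and no interval. Section 8.3.4 plans descriptions of primary and secondary endpoints by age class, AMH level, ovarian response and country. That list is open-ended, and site is not named in it.

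**Representativeness.** The outline, under Sample size, says that "the 15 sites expected to participate in the trial should be sufficiently representative to reflect the variety of practices" in the participating countries. Section 4.3 says that this number of sites "may be too limited to be representative and to reflect the variety of practices in the countries involved". Section 4.3 also accepts that prescribing could differ between centres and presents the limit of 15 women per site partly as a way to restrain a centre effect.

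**The concern.** The first sentence of section 8.1 presents 200 as chosen to secure a quality of estimate. Nothing in the protocol lets a reader judge whether it does, and the section's last sentence removes the usual basis for such a claim. The results would then appear as bare percentages, so the report would not show the precision either.

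The women are also grouped in 15 clinics. If clinics differ in GnRH protocol, trigger, luteal support or use of the dosing App, 200 women carry less information about general practice than 200 independent women would. A pooled percentage does not show by how much.

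The two statements on representativeness matter for the same reason. A reader of the outline is told that the sites reflect the variety of practice; a reader of section 4.3 is told that they may not. How far the findings on patterns of use can be generalised depends on which statement governs.

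**Working it through.** **Inputs from the protocol.** N = 200, 15 sites and at most 15 women per site (section 8.1); severe OHSS in about 1.4% of all stimulation cycles (section 1.1, background).

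**Input not in the protocol.** The intraclass correlation (ICC) within sites. It is assumed and shown as a range.

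**1. Can 200 be reproduced?** No, because no rate, width, alpha or power is stated. Only feasibility can be checked: 15 × 15 = 225 places, which is at least 200, and 200/15 = 13.3, so at least 14 sites are needed at the cap. A target of ±7 points around 50% would require 0.25 × (1.96/0.07)² = 196 women, close to 200, but the protocol names no such target.

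**2. Precision if women are independent.** Half-width = 1.96 × √(p(1−p)/200):
- p = 50%: ±6.9 points
- p = 30%: ±6.4 points
- p = 10%: ±4.2 points

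**3. Precision with clustering.** Mean site size m = 200/15 = 13.33. Design effect DE = 1 + (13.33 − 1) × ICC, and effective n = 200/DE. The half-width at 50% is q × √(0.25 × DE/200), with q = 1.96 (normal) or 2.145 (t on 15 − 1 = 14 degrees of freedom).

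| ICC (assumed) | DE | Effective n | ± points, normal | ± points, t on 14 df |
|---|---|---|---|---|
| 0 | 1.00 | 200 | 6.9 | 7.6 |
| 0.05 | 1.62 | 124 | 8.8 | 9.6 |
| 0.10 | 2.23 | 90 | 10.4 | 11.3 |
| 0.30 | 4.70 | 43 | 15.0 | 16.4 |
| 0.50 | 7.17 | 28 | 18.6 | 20.3 |

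Unequal site sizes change little. With 13 sites of 15 women and two sites of 3 and 2, the size-weighted mean is (13 × 225 + 9 + 4)/200 = 14.69. At ICC 0.30 the normal half-width is then 15.7 instead of 15.0 points.

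**4. A single site.** For 13 women at 50%, 1.96 × √(0.25/13) = ±27 points. Site-level figures can show spread, but they are not usable as estimates for a clinic.

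**5. Rare safety events.** If the background 1.4% applied here, 200 × 0.014 = 2.8 cases of severe OHSS would be expected, and the chance of none is 0.986²⁰⁰ = 6%. The exact (Clopper-Pearson) 95% interval for 3/200 is 0.3% to 4.3%; for 0/200 the upper limit is 1.8%.

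**6. Representativeness.** Both statements concern the same 15 sites and the same question, whether they reflect the variety of practice in the participating countries. The outline says they should; section 4.3 says they may not. The outline appeals to the total number of fertility centres in those countries but gives no number, so the text offers no way to decide between them.

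**The case against.** The strongest reply is that this is a declared descriptive study. The protocol says openly that the sample size has no inferential basis, claims no numerical precision, and leaves full methods to an SAP that is not available here. Leaving out intervals is then a choice and not an arithmetic error. That stands. It does not supply a basis for the opening sentence of section 8.1, nor settle the conflict between the outline and section 4.3.

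Three stronger readings are tempting, and the documents do not support them:

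- **That treatment patterns are mostly decided at clinic level.** The protocol says only that prescribing could vary by centre, and it gives no ICC. Daily dose is meant to follow each woman's AMH and body weight, and use of the algorithm is an inclusion criterion. The widened half-widths are therefore conditional on assumed values.
- **That only pooled results will be reported.** Country and other subgroups are planned on an open list, and a by-site description could be in the SAP. What can be said is that the protocol does not name one.
- **That the scarcity of severe OHSS would be hidden.** Counts are reported beside percentages, so a reader would see how few events there were. The 1.4% is also a background figure for all cycles, not a planning rate for this trial.

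The protocol also takes mitigating steps: the per-site cap, consecutive enrolment, and a mix of public and private sites. The cap limits any one site to 15/200 = 7.5% of the sample. It does not remove similarity between women within a site.

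**Conclusion.** The point holds in a limited form. Two defects lie in the text itself: section 8.1 says the size was planned to ensure meaningful estimates but gives no precision, and the outline and section 4.3 disagree on whether 15 sites are representative. A third matter is a stated choice that can be improved cheaply: as written, the reporting rules leave no place for an interval, since a confidence interval is ordinarily counted as inferential.

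The half-width of about 7 points at 50% requires independence between women. The range of about 9 to 19 points rests on assumed ICCs of 0.05 to 0.5 and a normal quantile. With t on 14 degrees of freedom it is about 11, 16 and 20 points at ICCs of 0.1, 0.3 and 0.5. The true ICC could differ by endpoint and may be near zero for some.

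Nothing here shows that 200 is too few for the descriptive aim. The documents simply do not say what precision it buys.

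**What to change.** 1. Reconcile the outline with section 4.3 by carrying the section 4.3 limitation into the outline's sample-size text.
2. Replace the opening claim of section 8.1 with the expected precision for N = 200, with and without clustering, and label the ICC values as assumptions.
3. Keep the statement that no hypotheses are tested, but allow descriptive 95% intervals. For GnRH protocol, trigger, luteal support, App use and the main outcome rates, use intervals that account for site, with a small-sample correction for 15 clusters. For rare safety events, use exact intervals.
4. Name the between-site spread of those treatment-pattern components as an output, shown as a range or plot and not as estimates for individual clinics.

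The cost is protocol and SAP wording and a few more tables, with no extra subjects or data. The stated precision will look less favourable than a bare percentage suggests.
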